## Abstract

**Background:**

Guidelines on modifiable risk factors regarding cardiological patients are poorly implemented in clinical practice perhaps due to low health literacy. Several digital tools for improving lifestyle and behavioural intervention were developed. Our primary aim is to evaluate the effectiveness of a digital exercise prescription tool on the adherence to physical activity recommendations among patients with cardiovascular diseases.

**Methods:**

A randomized controlled trial will be realized in cooperation with Cardiovascular Health Centres in Eastern Slovakia. Patients recruited through their cardiologists, will be randomised at 1:1 ratio to the three-months’ experimental condition or control condition. The experimental group will receive standard lifestyle consultation leading to individually optimized prescription of physical activity. The control group will receive standard, usual-cardio-care lifestyle counselling, also in the domain of physical activity. The digital system will be used for optimized exercise prescription. The primary outcome is a change in the patient’s adherence to exercise recommendations. Data will be collected in both groups prior to consultation and after 3 months.

**Discussion:**

This study protocol presents background and design of a randomized control trial to investigate the effectiveness of a digital system-provide exercise prescription tool on the adherence to physical activity recommendations. An optimized exercise prescription that better reflects patient’s diagnosis, comorbidities and medication can have a significant impact on secondary prevention of cardiovascular disease. This trial can provide important evidence about the effectiveness of digital exercise guidance in everyday practice of cardiovascular healthcare.

**Trial registration:**

The study was registered on 1st November, 2017 and is available online at ClinicalTrials.gov (ID:NCT03329053).

## Background

The age-standardised prevalence rate of cardiovascular disease (CVD) among the Slovakian male population (9,403 per 100,000) is the highest within the EU countries, while among females the comparable prevalence rate, approaching 7000 per 100,000, is the second highest across the EU member states [1]. In response to these statistics, a number of action calls are nowadays proclaimed for better and more effective prevention of CVD [2–6]. Exercise prescription is an essential part of primary and secondary CVD prevention programs.

Increasing exercise is clinically efficient in blood pressure management. A systematic review and meta-analysis of randomized controlled trials focused on the effects of exercise intervention in normotensive and hypertensive patients confirmed that resistance [7] and endurance [8] training lowers the systolic and diastolic blood pressure in patients with CVD. Exercise-induced hypertension reducing effects were confirmed in young [9], middle-aged [10] and elderly [11–13] population and also in patients with low responsiveness to hypertension medical treatment [14, 15]. Physical activity (PA) is seen as an effective modulator of the endothelial function [16], which was recognized as a main trigger of the cardioprotective effects of exercise [17–20]. Regular exercise performed by middle-aged and older healthy men should prevent age-associated loss in endothelium-dependent vasodilation and restore endothelial activity to levels similar to those of younger men [21]. Moreover, PA was able to attenuate the deleterious effect of nitric oxide synthase gene polymorphism on the systolic blood pressure [22] and has shown to have positive impacts on glycaemic control [23], cholesterol profile [24] and lipoprotein subclass profile [25].

To ensure maximal effectiveness and safety of exercise interventions [26, 27], experts in the field of cardiovascular health are regularly updating the guidelines containing recommendations for PA of patients with CVD. Between 2004 and 2006, the European Society of Cardiology (ESC) published miniseries of position papers that summarized specific recommendations for PA of patients by pathology [28–33]. A three-part miniseries published by the ESC in 2012 was describing the importance of PA and exercise modalities in the management of cardiovascular health. This time, exercise recommendations were dedicated for the general population [34], individuals with cardiovascular risk factors [35], and individuals with CVD [36]. The latest upgrade of ESC’s guidelines for PA was done in the year 2016 [37].

Despite the strong emphasis on regular exercise during lifestyle counselling [38], in the EUROASPIRE IV (European Society of Cardiology survey on the lifestyle, risk factor and therapeutic management of coronary patients), more than 59% of the interviewed patients reported little or no PA [39]. To clarify these conflicting observations, we need take to account the ecological factors [40], the quality of communication between care-providers and patients, [41, 42] and the patient’s skills to access, understand and use of disease-specific instructions and recommendations [43, 44]. The latter domain is also labelled as the patient’s health literacy (HL). The HL level influences the patient’s use of healthcare, quality of disease management and health risk behaviours [45] and reflects patient’s proactivity in attempting to utilize health literacy skills [43]. Sufficient HL is significantly associated with improved health outcomes with a lower cost of care [45], while HL inadequacies can compromise patient safety, worsen management of a disease and increase the incidence of health conditions requiring intense medical assistance or hospitalization [46]. In older adults, inadequate HL was significantly associated with poor implementation of PA recommendations [47]. For improvement of patient’s accessibility and applicability of health-related knowledge in real life, we need to emerge that patients and health professionals cannot address these needs independently [48].

For cardio-clinicians nowadays, the available time is very limited to implement all parts of the long versions of disease-, comorbidity-, and medication-specific guidelines for prevention of CVD [28–37]. Behavioural interventions mediated by a digital tool may be a feasible route to improve cardiovascular-related medication adherence and clinical outcomes [49–51]. For the improvement of exercise prescriptions accessibility and applicability in the secondary prevention of CVD, a digital support system for optimized exercise prescription seems to be appropriate. In response to this request, the European Association of Preventive Cardiology developed and introduced the Exercise Prescription in Everyday Practice and Rehabilitative Training (EXPERT) tool [52]. In this “utilization of physical activity recommendations among patients of cardiovascular healthcare centres” (AWATAR) trial, we will assess whether the EXPERT tool can effectively increase the utilization of exercise recommendations among patients with CVD. The effects of such a digital intervention may further be moderated by HL. Therefore, we will try to confirm that patients with higher HL might benefit more from the digital tool prescription compared with patients with lower HL.

### The aims of the AWATAR trial are therefore

to determine and compare the utilization of exercise recommendations after exercise prescription according to digital training and decision support system as compared to exercise prescription following the standard informative procedure among patients with CVD.to determine whether HL moderates the effect of exercise prescription according to the digital training and decision support system on the indices of exercise recommendations adherence among patients with CVD.

## Methods/design

### Trial design

To ensure complete reporting and sufficient replicability of our trial, we describe its design following the SPIRIT 2013 Statement [53] and create a schedule of enrolment, interventions, and assessments planned on the trial based on the SPIRIT template (Table 1). The AWATAR study will be the first randomized controlled trial (RCT) in which the utilization of exercise recommendations between the standard lifestyle informative procedure and the digital training and decision system informative procedure will be compared. Based on the reviewed literature, we hypothesize that a higher rate of adherence between the patient’s 3 months exercise report and patient’s digital tool exercise prescription will be observed in the experimental group compared with a three-months waiting group that receives care-as-usual. The trial protocol was approved by Human Research Ethics Committee of the Pavol Jozef Safarik University (approval no. PJSU-V-0825/17–1).

**Table 1 Tab1:** SPIRIT schedule of enrolment, interventions and assessments for experimental and control group in the AWATAR trial

	Study period		
Timepoint	Enrolment T_0_	Between T_0_ and T_1_	At three months T_1_
Enrolment:			
Eligibility screen	X		
Informed consent	X		
Allocation	X		
Intervention (either intervention under study or CAU)		#	
Assessments:			
Questionnaire on Adherence to recommendations	X		X
PA questionnaire	X		X
Anthropometry	X		X
Clinical data	X		X
Health literacy	X		X
Lifestyle variables	X		X
Socio-demographic data	X		X
Feasibility	X		X

(X - application of procedure in both experimental and control group; # - application of EXPERT tool in experimental group or application of standard informative procedure in control group)

### Participants

All potentially eligible participants from the cooperating Cardiovascular Health Centres (CHCs) will be screened and selected according the inclusion criteria exclusively through their cardiologists and receive written information about the trial. Within a week they will be contacted by phone to be provided by additional details about the trial and to confirm their availability to participate in the study. After telephonic agreement to participate in the study, they will be invited to an introductory session with the treating cardiologist. The cardiologist will review the inclusion criteria as indicated above and the exclusion criteria and discuss with the patient further study details. At a final formal step, a written informed consent form will be obtained from the participants. Following the introductory session, the baseline assessments of participants will be made.

### Inclusion criteria

The study aims at assessing the effects in routine care, i.e. for a wide age range and a number of cardiovascular diagnoses on inclusion criteria. To be eligible to participate in the AWATAR trial, patients have to meet following criteria:age between 40 and 75 years-old;ability to provide informed consent based on information about perceived health benefits and risks connected with participation in the study from the treating cardiologist;willingness to accept randomization and participation in the assessment procedures;presence of one or more below listed cardiovascular diagnosis (Table 2) at the recruitment moment of participants.

**Table 2 Tab2:** Inclusion criteria: present cardiovascular diagnosis at the recruitment moment of participants

Cardiovascular diagnosis	
coronary artery disease (both, with or without percutaneous coronary intervention)	
coronary artery bypass graft surgery, or endoscopic traumatic coronary artery bypass graft surgery	
compensated heart failure (with preserved or lowered left ventricular ejection fraction)	
cardiomyopathy	
intermittent claudication	
implantable cardioverter defibrillator or pacemaker	
ventricular assist devices	
heart transplantation	
valve disease or surgery	
congenital heart disease	
non-severe pulmonary hypertension	

### Exclusion criteria

After the participants’ inclusion, specific exclusion criteria regard minimization the risk of (sudden) exercise-induced cardiac events. Exclusion criteria include the presence of specific CVD problems that significantly increasing risks of sudden cardiovascular events, also identified as potential contraindications of PA on cardiovascular patients. These are summarized in Table 3-List A regarding specific cardiovascular conditions and List B regarding non-CVD specific exclusion.

**Table 3 Tab3:** Exclusion criteria: presence of specific cardiovascular conditions and non-specific exclusion criteria

List A	Presence of specific cardiovascular conditions
	uncontrollable hypertension
	decompensated heart failure
	severe and symptomatic aortic stenosis
	uncontrolled arrhythmia
	severe pulmonary hypertension
	acute coronary syndromes
	acute myocarditis, endocarditis, or pericarditis
	aortic dissection
	Marfan syndrome
List B	Presence of non-CVD specific exclusion criteria
	malignancy (active cancer) or life-threatening disease
	bed-bound patient status
	participation or plan to participate in other study during trial execution
	plan to move during the trial execution

### Randomization and allocation

The AWATAR trial will be realized as a two arm, parallel-group, randomized controlled trial with an allocation ratio of 1:1. Participants will be randomly assigned, with equal probability to fall into each of two trial arms into: the experimental group (EG) and the 3 months waiting list control group (CG). For the allocation process, a computer-generated allocation sequence will be prepared by an investigator with no involvement in the trial. Allocation sequence will be stratified by the cardiovascular diagnosis of participants and will not be disclosed to the cardiologists or persons from the investigation team participating in the trial. This important blinding step will prevent assignment of patients into EG or CG groups according to someone’s personal preferences.

For the assignment process, we will prepare identical, sealed, opaque, stapled envelopes, sequentially numbered by generated allocation sequence. Each envelope will contain the written code (EG or CG) indicating experimental or control group. This code containing envelope will be drawn by one member of investigatory team (AZ). The nature of the intervention makes it impossible to ensure blinding of the investigatory team or participants in presented trial settings.

### Intervention

#### Experimental condition

After baseline assessments, patients in experimental group (EG) will undergo behavioural counselling. During the 30-min long consultation EG patients will receive standard, usual-cardio-care lifestyle, hypertension and cardiovascular instructions, except recommendations for physical activities (PA). Instruction s on this PA domain will be provided exclusively through the digital training and decision support (EXPERT) tool. They will receive this information immediately after the baseline assessments by a trained member of the investigatory team (AZ).

The EXPERT tool is an interactive digital training and decision support system for optimized exercise prescription in cardiovascular disease patients. The tool was developed by a working group connecting 33 experts in the rehabilitation of chronic internal diseases and three computer science experts from 11 European countries. During the construction of the system, clinical and rehabilitation experts reviewed all relevant and accessible recommendations, current clinical guidelines, studies and expert opinions in exercise intervention of cardiovascular patients. Specific exercise intervention goals were formulated for each different CVD, CVD risk factor and other chronic non-cardiovascular comorbidity.

The EXPERT tool was designed to provide optimized exercise prescription based on detailed overview of patient’s diagnosis, prognostics, complications and medication. The digital system requires data input in four steps, the data about patient’s clinical and cardiological characteristics (parameters), patient’s medication data and data summarizing patient’s adverse events registered during exercise testing. The EXPERT tool is able to generate exercise prescriptions even some of the relevant parameters are missing. In this case, unavailable data are not reflected in the prescription process and should negatively affect individualization and optimization rate of recommendations for patient in final.

After execution of the required data input, the EXPERT tool is ready to generate an exercise prescription (type of exercise) defining five regulatory parameters: 1) intensity and 2) frequency of the exercise, 3) duration of each exercise session, 4) duration of the training program, 5) feasibility of the strength training during the training program. Additionally, the prescription contains exercise contraindications and safety precautions for a certain type of exercise. The generated exercise prescription will be explained and discussed in details by a member of the investigatory team and will be printed in two paper copies for the patient. We will forward the EXPERT tool’s output in electronic form to patient’s email address. All outputs will be safely stored for replication or exercise prescription history review.

#### Control condition

Patients randomized to the (3 months waiting) CG will after baseline assessment receive standard, usual-cardio-care lifestyle, hypertension and usual cardiovascular instructions, so also in the domain of recommendations for physical activities. The exercise prescription process during consultation in the CG will be constructed in accordance with published ECS guidelines and recommendations for CVD secondary prevention [54]. The timing and mediator of behavioural counselling of the CG will be same as on the EG. Participants in CG will be informed, that after expiration of 3 months control period, and they will be offered to receive an identical digital-based (EXPERT) exercise prescription as patients in EG. Through the intervention all participants are instructed to maintain the standard treatment. Patients who declined to participate in the trial and those who will cancel participation during implementation of the trial will be asked to complete a short questionnaire to collect basic socio-demographic and behavioural data and explore the reasons for non-participation or non-continuation in the trial.

### Procedure

Assessments will be conducted at two time points – (prior to patient’s behavioural consultation and 3 months follow-up the consultation). Completion of measurements should take maximally 30 min. One member of the investigatory team (AZ) will perform all measures in the trial. A dedicated member will undergo a training session to ensure consistency of assessment protocol and validity and reliability of applied diagnostics instruments.

### Primary outcome measures

The *primary outcome* is exercise recommendations adherence as assessed by agreement between the patients reported and the prescribed indices of exercise. The indices are type, duration, intensity and frequency of exercise. Patient-reported type, duration, intensity and frequency of exercise will be assessed using a short self-report questionnaire (Table 4), reflecting the construction and definition of exercise prescriptions generated by the EXPERT tool. The questionnaire will be filled with assistance of an investigatory team member and he will ask participants to report regularity on exercise over the last year and describe in detail the type, duration, intensity and frequency of exercise realized over the last 3 months. Exercise recommendations adherence will be determined as agreement between indices of exercise prescription delivered by EXPERT tool and self-reported indices of exercise performed in monitoring period (3 months). In the follow up assessment, the last section of the questionnaire will be dedicated on the general evaluation of PA behavioural change (by the question: “Have you registered a change in your PA behaviour during the last three months?”; with options for answer: “Definitely/Partially/Only limited change/Not at all”).

**Table 4 Tab4:** Measurement dimensions of exercise recommendations adherence and outcome variables

Measurement dimensions	Outcomes variables (independent data for last 3 months recall period)
Type of exercise	• Endurance training (walking, bicycling, swimming) • Strength training (free weight or resistance strength training, weightlifting) • Speed training (all short duration exercises with high intensity) • Anaerobic training (all exercises generating “lactate feelings”) • Sport games or mixed/other training
Duration of exercise (in one session)	• 0–10 min. • 10–20 min. • 20–30 min. • 30–45 min. • 45–60 min. • 60–90 min. • 90–120 min. • 121 and more min.
Intensity of exercise (typical intensity)	• Light Activity: an activity that does not cause you to ‘huff and puff’. • Moderate Activity: an activity that makes you breathe harder than normal, but only a little. • Vigorous Activity: an activity that makes you ‘huff and puff’.
Frequency of exercise (per week)	• Daily • 3–6 per week • 1–2 per week

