### Data analysis

All data analyses will be carried out using statistical software package IBM SPSS 22.0 or equivalent. Analyses will include standard descriptive statistics, Pearson chi-squared test for categorical variables, independent- and paired-sample tests of differences for continual variables (e.g. t-test/U-test, ANOVA) adjusted for baseline values. The agreement between indices of exercise prescription delivered by EXPERT tool and self-reported indices of exercise performed in monitoring periods will be tested using intra-class correlation test. Modelling of associations with possible adjustments will be conducted with regression analysis (linear and/or binary logistic). Analysis will be performed primarily based on intention-to-treat. In addition, a per-protocol analysis including only patients with no missing observations of the variable of interest will be performed. All tests will be two-tailed with statistical significance set at an α level of 0,05.

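### Adherence is defined against the EXPERT prescription, which controls are offered only after the 3-month control period, so the primary comparison favours the EXPERT arm wherever the two prescriptions differ

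*Protocol article*

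**What the plan says.** The protocol article describes the primary outcome in two ways. Primary outcome measures opens with a general form, "agreement between the patients reported and the prescribed indices of exercise", which does not say whose prescription is meant. Sample size uses similarly general wording. The same outcome section then gives the only operational rule: "adherence will be determined as agreement between indices of exercise prescription delivered by EXPERT tool and self-reported indices of exercise". Data analysis repeats that comparator: "The agreement between indices of exercise prescription delivered by EXPERT tool and self-reported indices of exercise performed in monitoring periods will be tested". The hypothesis under Trial design carries it across the arms, expecting that a higher rate of agreement with the patient's "digital tool exercise prescription will be observed in the experimental group compared with a three-months waiting group that receives care-as-usual".

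Controls are given something else. Their exercise advice at the baseline consultation "will be constructed in accordance with published ECS guidelines and recommendations for CVD secondary prevention". They are told that "after expiration of 3 months control period, and they will be offered to receive an identical digital-based (EXPERT) exercise prescription". Under Experimental condition, the other arm gets its physical activity instructions through EXPERT alone. Procedure and Table 1 place the second assessment at 3 months, and the questionnaire asks about exercise over those 3 months.

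The first aim is "to determine and compare the utilization of exercise recommendations after exercise prescription according to digital training" and decision support, compared with prescription by the standard informative procedure.

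**The concern.** Adherence ordinarily means doing what one was advised to do. Under the operational rule, only the EXPERT arm has been shown the standard it is judged by. A control who follows the advice received to the letter still counts as non-adherent on every index where that advice differs from EXPERT. Alternatively, no EXPERT prescription exists for the control at 3 months, and there is no score to compare.

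The primary result would then mix two things: how well patients follow advice, and how far the two sets of advice differ. A difference in favour of EXPERT could come from the second alone. Aim 1 concerns the use patients make of recommendations after each type of prescription, and the primary outcome as operationalised would not isolate that.

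**Working it through.** **1. Which prescription scores which arm**

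| Section | Comparator named | Consequence for controls |
|---|---|---|
| Trial design (hypothesis) | Digital tool prescription, compared between arms | Scored against EXPERT |
| Primary outcome measures, opening | Prescribed indices, source not named | Open |
| Primary outcome measures, operational rule | EXPERT prescription | Scored against EXPERT, or no score |
| Sample size | Prescribed indices, source not named | Open |
| Data analysis | EXPERT prescription | Scored against EXPERT, or no score |
| Control condition | Advice given is guideline-based; EXPERT offered after 3 months | EXPERT content not seen during the recall period |

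No section scores controls against the advice they received. Even if EXPERT were handed over at the 3-month visit itself, it could not have guided the exercise being reported.

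**2. The scale for comparison**

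Sample size gives an effect of 0.33, 80% power and two-sided α of 0.05. The usual formula gives 2 × (1.960 + 0.842)² / 0.33² = 2 × 7.85 / 0.1089 = 144.2, so 145 per arm. The article's effective size is 144 per arm, at which power is 79.96%. The 0.33 therefore behaves as a standardised mean difference, and a spurious difference can be set against it on that scale.

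**3. Illustration of size**

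None of these inputs is in the documents; all are assumptions:
- a: probability of following one's own advice on an index, equal in both arms, 0.5 to 0.7.
- q: proportion of indices on which control advice differs from EXPERT, 0.10 or 0.25.
- 1/3: probability that a control who does not follow differing advice matches EXPERT by chance.
- Score: number of matches over four independent indices.

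Match probabilities per index are π_E = a and π_C = (1 − q)a + q(1 − a)/3. With v the mean of π(1 − π) over the two arms, d = 4(π_E − π_C)/√(4v) = 2(π_E − π_C)/√v.

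| a = π_E | q | π_C | π_E − π_C | √v | d |
|---|---|---|---|---|---|
| 0.5 | 0.10 | 0.467 | 0.033 | 0.499 | 0.13 |
| 0.7 | 0.10 | 0.640 | 0.060 | 0.469 | 0.26 |
| 0.5 | 0.25 | 0.417 | 0.083 | 0.497 | 0.34 |
| 0.7 | 0.25 | 0.550 | 0.150 | 0.478 | 0.63 |

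The true difference in adherence is zero in every row. The per-index gap is q[a − (1 − a)/3]. It is zero only if q = 0 or a = 0.25, and it favours EXPERT for any a above 0.25.

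**4. Sensitivity to the chance-match assumption**

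Now let patients in either arm who do not follow their advice match EXPERT with probability 0.25. Then π_E = a + 0.25(1 − a) and π_C = a(1 − q) + 0.25(1 − a). At a = 0.5 and q = 0.10 this gives 0.625 against 0.575, so d = 0.20, with about a 41% chance of a significant result at 144 per arm. Over a from 0.3 to 0.7 and q from 0.10 to 0.50, d runs from 0.12 to 1.53. It is again zero at q = 0.

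**5. Scoring each arm against its own prescription**

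In the model of step 3, both arms then match with probability a, and the expected difference is zero.

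**The case against.** **The wording is not uniform.** Two places speak only of prescribed indices, so a reader who infers that the article settles beyond doubt that both arms are scored against EXPERT goes further than the text. This stands. But the only operational rule names EXPERT, the hypothesis compares the arms on it, and nothing offers an alternative for controls. The ambiguity itself needs resolving.

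**Controls need not be unscorable.** Table 1 shows clinical data collected at baseline in both arms, so an EXPERT output could be produced for a control, and the timing may be in the full protocol. This also stands. It leads, however, to the other outcome: a score against a prescription that the control was not shown.

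**A common yardstick is legitimate.** EXPERT was built from a review of clinical guidelines, and control advice is guideline-based. Agreement with EXPERT could be taken as closeness to well-targeted exercise, with better targeting counted as part of the effect. That is a coherent outcome, but it is not the adherence that the article names, and only one arm is shown the yardstick.

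**The size is assumed.** This stands in full. Overlap between the two sources could be large. The exact-match count is a device for illustration. Data analysis names an intra-class correlation, which may credit near-agreement on ordered categories. The four indices may also be correlated.

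**The article is condensed.** That excuses missing detail. It does not excuse a comparator that is stated and does not fit one of the arms.

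**Conclusion.** The concern holds in a limited form. The operational definition, the hypothesis and the analysis all point to EXPERT as the comparator, while controls are advised from another source during the whole recall period. As written, controls have no score or are scored against advice they were not shown. With equal adherence in the range illustrated, the comparison leans towards the EXPERT arm wherever the prescriptions differ, and a positive primary result could not be read as better adherence.

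Two stronger readings are tempting and unsupported. A reader might infer that the bias would supply the whole design effect. It does so in some illustrated cases (0.34–0.63 at 25% of indices differing) and not in others (0.13–0.26 at 10%), and the documents do not say how far the prescriptions differ. A reader might also infer that the trial could say nothing about the tool's effect. It also collects outcomes not tied to EXPERT, such as the question on perceived change in activity, blood pressure, lipids and peak oxygen uptake. The defect lies in the primary comparison, and it should be corrected before that comparison is used.

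**What to change.** 1. Record the exercise prescription given at baseline in both arms on one form with the four indices: type, duration, intensity and frequency.
2. Define the primary outcome as agreement between the reported indices and the prescription that the participant received. Align Trial design, Sample size, Primary outcome measures and Data analysis to that definition.
3. Add an arm-neutral secondary outcome from the Table 4 questionnaire, namely reported exercise frequency and session duration. IPAQ-SF should not carry this role, because Secondary outcome measures directs it at activity such as gardening and housework that does not count as sport or performance-oriented exercise.
4. If agreement with EXPERT is kept, make it secondary. Generate the control output from stored baseline data only after control counselling and the 3-month assessment are complete. Control condition and Monitoring indicate that the same team member counsels and assesses both arms. Earlier output could therefore influence the control advice, even if withheld from patients.

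The cost is revised wording and one short form. If item 4 is adopted, EXPERT data entry is also needed for all assessed controls, including those who decline the later offer. The main downside is that the two prescriptions may differ in difficulty or vagueness, and looser advice is easier to match. Item 3 helps to reveal this but does not remove it.
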